### Interventions

Each selected elderly centre will be randomly assigned to either IGs or CG and asked to help to recruit participants with a sample size of 14–15 older adults. There will be 16 centres in the IGs to receive four combinations of three training modes (A: cognitive training only, B: physical training only, C: CCPT) and with 4 centres in IGs. The four types of combinations are 1. Mixed ABC, 2. A + B, 3. B + C, 4. C + A, matched with 4 CGs in total. For the case of combination 1. Mixed ABC, participants will receive different training modes every 2 consecutive weeks with randomized order. For the case of combinations 2, 3, and 4, the participants’ centres will receive an assigned sequential order of two training modes with each mode lasting for 2 months. All participants of IGs will attend training sessions twice a week, and 60 min duration per session (per mode). The random allocation sequence of intervention was generated by a blinded statistician external to the research team. Due to the nature of each intervention, blinding cannot be applied to the participants, while the blinded group allocation will be applied to the data assessors and analysts. Each subject will be identified by the number code. Data from those participants having more than 70% attendance will be analyzed. No further follow-up with missing cases will be done because they will be usually missing at random (such as absences due to doctor’s appointments or being sick).

The three training modes (A, B, and C) are introduced as follows:A: Cognitive training only

The cognitive training program will have the participants playing board games in groups. The selection criteria for the board games are: involving a group of 2–4 players, requiring thinking skills in playing, being relatively easy to learn to play and being a fun game. Ten popular commercial board games are selected (Dominos, Yahtzee, Pavilion, Scopa, UNO, Rummikup, Charades, Cranium, Gabblet, Chinese Checker – see Additional file 1 for a brief description). The training format of board games consists of these essential elements as program strategies: having social support, fun, high repetition, and practice, which are deemed to be important by researchers [6] in designing intervention programs. During each intervention session, participants will engage in four randomly assigned games out of the ten games. They will be randomly put in groups with each group engaging in one game for 15 min of playtime. Also, in the last 5 min of each session, participants will be asked to share feedback about the games. An instructor and an assistant recruited from the centre will help to monitor the board games practice in a 60 min session. The elderly centre staff will be trained for 3 h to play and understand the instructions and rules of the board games to be offered to the participants.B: Physical training only

The physical training program will involve learning three preselected routines of ‘Line dancing’ (see Additional file 2 for a brief description of a sample dance). The current program aims to improve the cardiorespiratory endurance of older adults by learning sequences of walking and turning rhythmic moves with music in a structured group exercise setting. Participants will learn each routine in 5 lessons. The last lesson will be spent on revising all 3 routines. Prior to the start of the study, a panel of three experienced line dancing instructors with experience in teaching older adults will select three-line dancing routines for this program. The panel will help to develop three instructional lesson plans. Moreover, three separate pilot trials of teaching the pre-selected dance routines will be conducted with a group of 10 participants. These participants will wear a Polar heart rate monitor to get heart rate data during training at pilot trials so that the moderate-to-vigorous intensity levels and the targeted heart rate zone (according to ACSM guidelines on exercising intensity for older adults [22]) can be documented. The format of training in a session will include 10 min warm-up, 45 min main training, and 5 min cool-down. One major instructor with one assistant will lead the prescribed activities for a ratio of 1 leader to 7–8 older adults to ensure adequate instruction and supervision of the participants. ‘Line dancing’ certified instructors will be recruited either from the Hong Kong Line Dancing Association, other dance associations, or through media. The ‘Line dancing’ instructor has to attend a 2-h refresher course on the instructional lesson plans of the three preselected line dance routines.C: Combined cognitive and physical training (CCPT)

This program will adopt the BIGMAP which was trialed out with older adults in the community elderly centres by data collection of nonverbal Stroop test on cognition, functional fitness test based on senior fitness test and heart rate data. This program provided a set of ten cognitive games combined with physical training with various difficulty levels [5] designed by cognitive psychologists and exercise scientists. Each game is targeted to improve on cognitive functions by training on visual, spatial, hearing memory, and proprioception as well as physical fitness functions through physical and motor skills training on moderate-intensity aerobics activities, muscular endurance, balance, reaction, and coordination [15] (see Additional file 3 for descriptions of BIGMAP). Based on empirical evidence, BIGMAP involves moderate intensity of aerobics training (mostly of walking activities) to the participating older adults. One major instructor with two assistants will lead the prescribed BIGMAP activities (including physical training and cognitive games) for a ratio of 1 leader to 5 older adults to ensure adequate instruction of the participants. A three-hour off-site classroom training and one-hour on-site training will be offered by an experienced supervisor involved with previous BIGMAP study to the instructor and assistant of the CCPT mode following the training manual of BIGMAP [15].

In regards to the monitoring of the instructors’ quality, a supervision procedure will be applied to all training modes that is having an experienced trainer observing the first session of an intervention program to ensure proper instruction in both phases of the study. Therefore, the instruction quality of each training mode will be affirmed.

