### Participants recruitment

Eligible elderly participants (age 60 or above) who have passed a cognitive and emotional screening test will be recruited by the community centres with preset inclusion and exclusion criteria. The demographic information of all participants will be collected in terms of age, educational level, medical history, living conditions, occupation, and daily activity patterns. All participants will be informed of the objectives, potential risks, benefits and the data collection procedure of the study. They will sign a written consent prior to their participation.

The inclusion criteria of participants include willingness and capability to give informed consent to participate in the training and testing of this study; and pass the cut-off of the screening tests (cognitive and emotional): Montreal Cognitive Assessment Test (MoCA), a widely used assessment test for cognition [21], with the score above 19 (satisfactory basic function). The elderly will be excluded if s/he has a history of systematic cardiovascular diseases causing cognitive impairments, poorly controlled hypertension, stroke, Parkinson’s disease, early stages of Alzheimer’s disease, brain injury or brain operations, and other complicated conditions that could have prevented attending regular attendance and taking assessments in the elderly centre; concurrent major psychiatric disorder (e.g. major depressive disorder, schizophrenia) or drug and alcohol abuse; and currently receiving regular physical (perform aerobic, flexibility, and stretching exercises for 3 days per week, 45 min per session, for 1 year or longer) and cognitive exercises (such as playing mahjong, chess, bridge, and reading for more than 30 min per session and 3 times per week, for 1 year or longer).

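### Centres are assigned to an arm and recruit their own participants, with no stated masking of recruiters; the plan thus permits enrolment with the arm known, chiefly threatening intervention versus control

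*Protocol article*

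**What the plan says.** Under Interventions: "Each selected elderly centre will be randomly assigned to either IGs or CG and asked to help to recruit participants", with 14–15 older adults per centre. Under Participants recruitment, eligible people "will be recruited by the community centres with preset inclusion and exclusion criteria". The randomised clusters thus fill their own places.

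On masking, Interventions says that "blinding cannot be applied to the participants, while the blinded group allocation will be applied to the data assessors and analysts". Staff who recruit are not mentioned. On the sequence: "The random allocation sequence of intervention was generated by a blinded statistician external to the research team". This covers how the sequence is produced, not when a centre learns its arm.

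One inclusion criterion is "willingness and capability to give informed consent to participate in the training and testing of this study". Under Research design, control participants carry on as usual and attend four assessments. The description of cognitive training adds: "The elderly centre staff will be trained for 3 h to play and understand the instructions and rules of the board games".

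The Fig. 1 caption names recruitment ahead of allocation. The figure itself is not available here.

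**The concern.** Randomising centres balances the arms, on average, for people who would have entered whatever the arm. If people are approached, or decide, after the arm is known, those who enter can differ by arm, and randomisation no longer protects the comparison. A centre with four months of free group training to offer may draw different volunteers from a centre that can offer only repeated testing. Eligibility criteria limit who may enter, not who is approached or agrees. A larger sample would estimate the biased contrast more precisely without removing the bias.

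**Working it through.** **1. Order and masking, side by side**

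- Interventions: the centre is assigned and asked to recruit.
- Participants recruitment: the centres do the recruiting.
- Blinding: assessors and analysts yes, participants no, recruiters not mentioned.
- Centre staff are trained in the board games, so staff at a centre receiving mode A learn this at some point. The date relative to recruitment is not given.
- No running text places consent or T1 before disclosure of the arm.

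Knowledge of the arm at enrolment is thus permitted and plausible, but not stated.

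**2. Where appeal differs between arms**

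The four combinations are Mixed ABC, A + B, C + A and B + C. Each of A, B and C appears in three of the four, and every combination includes some physical activity, through B or C. C + A lacks line dancing and B + C lacks board games; the remaining contrasts are milder. The control arm offers no training at all, so the sharp difference in appeal is IG versus CG.

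**3. The plan's sample size reproduces**

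Inputs from Sample size: f = 0.175, alpha 0.05, power 0.90, rho 0.5, 5 groups, 4 measurements. For the group-by-time interaction, λ = N f² m/(1 − rho) = 95 × 0.030625 × 4/0.5 = 23.3, on (5 − 1)(4 − 1) = 12 and (95 − 5)(4 − 1) = 270 degrees of freedom. Power is 0.909. The smallest N is 93, or 95 with equal groups. Then 1 + 14 × 0.1 = 2.4; 95 × 2.4 = 228; 228/0.8 = 285; 285/20 = 14.25 per centre. The trial is therefore sized for the interaction.

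**4. What a recruitment shift does to each contrast**

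Suppose selective recruitment moves one arm by a constant δ at every visit.

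- Effect averaged over T1 to T4: (δ + δ + δ + δ)/4 = δ. The shift passes through in full.
- Change from T1: δ − δ = 0. The shift cancels.

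If the recruits in one arm would also change differently by γ, for example through motivation or response to training, the change contrast carries γ.

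The Statistical analysis plan section has T1 as one level of Time and puts its focus on between-group differences, without saying whether that means the main effect or the interaction.

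**5. Scale (assumed shifts only)**

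The documents give no shift. Moving one of five equal arms by d SD gives f = √{[4(d/5)² + (4d/5)²]/5} = 0.4d. An assumed 0.1 to 0.3 SD is then f = 0.04 to 0.12, below the planning value of 0.175, which on this pattern corresponds to 0.175/0.4 = 0.44 SD.

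As an illustration, take no treatment effect, an unadjusted comparison of centre means, ICC 0.1 and 228/20 = 11.4 analysed per centre. The variance of a centre mean is 0.1 + 0.9/11.4 = 0.179. The standard error is √(2 × 0.179/4) = 0.299 for 4 versus 4 centres, and √(0.179/16 + 0.179/4) = 0.236 for 16 versus 4. Rejection rates of a two-sided 5% test, from the noncentral t:

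| Assumed shift | 4 v 4 centres (df 6 to 15) | 16 IG v 4 CG (df 18) |
|---|---|---|
| 0.1 SD | about 6% | about 7% |
| 0.2 SD | 9–10% | about 13% |
| 0.3 SD | 14–16% | about 22% |

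These rates apply only if the shift falls on the compared outcome. They are not estimates for this trial.

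**The case against.** The strongest reply is that the text never says recruiters or participants know the arm. The sentence joins assignment and recruitment with a plain conjunction, the Fig. 1 caption gives the opposite order, and an article may leave concealment steps to the full protocol. The remark on participant blinding is tied to the nature of the training, so it concerns receiving the intervention, not knowledge at enrolment. This stands against any claim that T1 is certainly taken with the arm known. It does not remove the point: recruitment in the caption may mean recruitment of centres, and the only running text on the order puts assignment first.

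A reader might also infer that a dancing arm is being compared with a board-game arm. No such arms exist, and the overlap of modes weakens the argument among the IGs.

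Safeguards exist too. Eligibility criteria are preset, people already in regular exercise and cognitive activity are excluded, demographic data and T1 are collected, and evaluators are blind. These limit or reveal part of an imbalance, so it would be too strong to say that bias could never be distinguished from a treatment effect. They do not stop people choosing to enter because of the arm on offer.

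Finally, one might set a shift of 0.1 to 0.3 SD directly against f = 0.175. The two are on different scales, and the shift has no source in the documents.

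**Conclusion.** The point holds in a limited form. As written, the plan permits recruitment and consent with the arm known, and it names no step that prevents this. That recruiters and participants will know the arm is an inference from the stated order and the list of who is blinded. The IG–CG comparison is most at risk; comparisons among the four IGs are at lower risk.

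The consequence depends on the contrast used: a stable level difference biases an effect averaged over all four visits and drops out of the group-by-time interaction, while differential change biases both. The size of the bias cannot be derived from the documents, and the rates tabulated above show only how sensitive an unadjusted comparison would be. The point merits a change because selection at entry is hard to repair in analysis and the remedy is mainly a re-ordering of existing steps.

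**What to change.** In Participants recruitment and Interventions, state that in each phase all 10 centres identify, screen and consent participants and complete T1 before the external statistician releases that phase's allocations. Use one neutral invitation that describes all five possible assignments. If this is already the practice, correct the sentence in Interventions and give the point of disclosure.

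In the Statistical analysis plan section, base the IG–CG and between-IG comparisons on change from T1, that is, on the group-by-time contrast, and not on the main effect averaged over T1 to T4. T1 is already a level of Time, so the model needs no new term, and this is the test that the sample size of 95 before clustering matches.

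No extra staff or procedures are needed, but timing suffers. About 285/2 ≈ 143 people per phase, each tested for under 2 hours, would have to finish T1 first: up to about 285 assessment hours before any centre learns its arm. Instructor booking and staff training would come later, there would be a gap between T1 and the first session, and some people will decline without knowing their arm.

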### Research objectives and hypothesis

The purpose of this study is twofold: first, to determine the effectiveness of four mixed modalities, namely Mixed ABC, A + B, C + A, and B + C, of three training programs (A: cognitive training, B: physical training, and C: combined cognitive and physical training (CCPT)) on cognition, fitness, and psychosocial-related health of community-dwelling older adults in Hong Kong; and second, to determine which specific training program being most effective among the three programs as compared to the control group (CG).

The hypothesis is that participants with the integrated format of three training modes will have higher cognition and fitness scores than the participants with the other combinations of two training modes, and all these mixed modalities will show greater positive outcomes than the control group.

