## Methods

### Research design

This study is a cluster randomized controlled trial (CRCT), to be carried out in 20 community elderly centres (see Fig. 1). The elderly centres will be randomly selected from the population list of elderly service providers in the 18 districts of Hong Kong and assigned to either one of the 4 Intervention Groups (IGs) or the Control Group (CG). There will be 16 centres in the IGs and 4 centres in the CG participating in a 6-months program (4-month intervention with 2-month follow-up). The 20 participating centres will be equally allocated to two Phases, I and II, with each Phase involving 8 centres in IGs and 2 centres in CG. Each IG will be randomly assigned to one of the four combinations of three training modes that include cognitive (A), physical (B), and combined cognitive and physical training (CCPT, i.e. C), namely Mixed ABC, A + B, C + A, B + C. The intervention will last for 4 months in which the training is conducted for 16 sessions, 2 sessions per week, and 60 min per session.

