**Fig. 1 Fig1:**
[figure not shown]
Flow diagram of the study through two phases of the CRCT, including recruitment, allocation, intervention, and data collections points

In each phase, four repeated assessments (T1-T4) will be conducted: T1 is the pre-test before intervention; T2 and T3 will be conducted on intervention right after the end of 2-month and 4-month, respectively; T4 is a follow-up test conducted 2 months after the completion of all intervention training. Participants of CG will be asked to assume regular-daily habitual activities and take four repeated assessments only.

The study is designed in accordance with the SPIRIT (Standard Protocol Items: Recommendations for Interventional Trials). The study protocol has been approved by University Research Ethics Committee (REC/19–20/0066) and registered at ClinicalTrials.gov Identifier: NCT04727450.

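### The three-modes-versus-two hypothesis is fully aliased with the delivery schedule, because Mixed ABC is the only arm that changes mode every 2 weeks

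*Protocol article*

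**What the plan says.** In the protocol article, Research objectives and hypothesis, the first half of the prediction reads: "participants with the integrated format of three training modes will have higher cognition and fitness scores than the participants with the other combinations of two" (that is, of two modes). It describes the arms by how many modes they contain and does not mention the schedule.

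The Interventions section lists the arms: "The four types of combinations are 1. Mixed ABC, 2. A + B, 3. B + C, 4. C + A, matched with 4 CGs in total". It then sets two delivery patterns. For the three-mode arm: "For the case of combination 1. Mixed ABC, participants will receive different training modes every 2 consecutive weeks with randomized order". For the three two-mode arms: "the participants’ centres will receive an assigned sequential order of two training modes with each mode lasting for 2 months". Session frequency and length are common to all intervention arms: "All participants of IGs will attend training sessions twice a week, and 60 min duration per session (per mode").

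On timing, Research design says: "The intervention will last for 4 months in which the training is conducted for 16 sessions, 2 sessions per week, and 60 min per session". For the assessments: "T2 and T3 will be conducted on intervention right after the end of 2-month and 4-month, respectively". T4 follows 2 months after training ends.

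The Statistical analysis plan section fits a five-level group factor and a four-level time factor, with centre as a random effect. It places the main focus on differences among the four intervention groups.

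**The concern.** The hypothesis invites the reader to credit any advantage of Mixed ABC to the third mode. Every comparison that could show such an advantage also sets short rotating blocks against long sequential ones. A positive result could come from frequent switching or variety, and a null result from blocks too short to build on. Neither would tell us whether three modes are better than two. Randomising centres does not help: it balances the centres, but it cannot separate two features that are bundled within one arm.

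The early assessment adds a second difficulty. It falls at the point where the two-mode arms change over, so a difference seen there between Mixed ABC and a two-mode arm is not a three-versus-two difference.

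**Working it through.** The plan gives no figure for this point. The sample size is not in question and reproduces: design effect 1 + (15 − 1) × 0.1 = 2.4; 95 × 2.4 = 228; 228 / 0.8 = 285.

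**Step 1: set the arms side by side (Interventions).**

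| Arm | Number of modes | Schedule |
|---|---|---|
| Mixed ABC | 3 | change every 2 weeks, randomised order |
| A + B | 2 | two sequential 2-month blocks |
| B + C | 2 | two sequential 2-month blocks |
| C + A | 2 | two sequential 2-month blocks |

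No arm gives three modes in long blocks, and none gives two modes in 2-week rotation.

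**Step 2: estimability.** Let M = 1 for three modes and 0 for two, and let S = 1 for 2-week rotation and 0 for 2-month blocks. Over the four arms in the order above, M = (1, 0, 0, 0) and S = (1, 0, 0, 0). The columns are identical, so a contrast of Mixed ABC with a two-mode arm estimates the sum of the two effects and never either one alone. Adding a schedule term to the planned model would not help, because schedule is fixed by arm.

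**Step 3: how far the schedules differ.** The inputs are 4 months, 16 sessions and 2 sessions per week (Research design). These do not fit together: 16 / 2 = 8 weeks, not 4 months. Both readings are therefore shown, with 4 months taken as 16 weeks (an assumption).

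| | 16-week reading | 8-week reading |
|---|---|---|
| Total sessions | 16 × 2 = 32 | 8 × 2 = 16 |
| Two-week blocks in Mixed ABC | 16 / 2 = 8 | 8 / 2 = 4 |
| Switches in Mixed ABC, at most | 8 − 1 = 7 | 4 − 1 = 3 |
| Switches in a two-mode arm | 1 | 1 |
| Mean sessions per mode, Mixed ABC | 32 / 3 = 10.7 | 16 / 3 = 5.3 |
| Sessions per mode, two-mode arm | 32 / 2 = 16 | 16 / 2 = 8 |

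**Step 4: what each arm has received at T2.** T2 is at 2 months. Under the Interventions section each two-mode arm has by then completed its first mode and not begun its second, so it has received one mode. On the 16-week reading Mixed ABC has had four 2-week blocks. Whether those four cover all three modes depends on how the order is randomised, but the two-mode arms have had a single mode in any case. T3 and T4 are the assessments at which every intervention arm has had its full set of modes.

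**Step 5: scope.** Four intervention arms give 4 × 3 / 2 = 6 pairwise comparisons. The three that include Mixed ABC are affected. The three among the two-mode arms share one schedule and are not. The four comparisons of an arm with control remain valid as comparisons of whole packages.

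**The case against.** The best defence is that the trial tests named programmes. The first objective refers to four mixed modalities by name, and words such as mixed and integrated can be read to include the interleaving that the Interventions section states openly. On that reading the contrast is a legitimate comparison of packages. This stands as a reading of the design. It does not rescue the hypothesis sentence, which sets three modes against two and says nothing of schedule. It is in effect an argument for the rewording.

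The block schedule also has a purpose. Two-month blocks line up with T2 and T3, which suits the second objective of estimating the effect of each mode. That is a good reason to leave the schedule alone.

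Three stronger readings are tempting, and the documents do not support them:

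- *That Mixed ABC participants are tested with every mode more recently trained.* This needs a regular rotation, and the order is randomised. On the 16-week reading, the block sequence A, B, C, A, C, B, C, B last gives mode A in block 4, ending at week 8. The gap to T3 is 16 − 8 = 8 weeks, the same as for the first mode of a two-mode arm. No recency difference is claimed here.
- *That the article already commits to concluding that three modes beat two.* The anticipated conclusion in the abstract compares the integrated format with single modes, and the mixed modalities with control. The problem lies in the hypothesis sentence.
- *That aligning the schedules would isolate the number of modes.* It would not. At a fixed total, a third mode still lowers the sessions per mode (10.7 against 16, or 5.3 against 8), and three 2-month blocks would take 6 months, not 4.

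**Conclusion.** The point holds as a limit on interpretation. In all three contrasts of Mixed ABC with a two-mode arm, number of modes and delivery schedule are completely aliased, and no analysis of these arms can separate them. This follows from the Interventions section alone and needs no assumption. The size of the schedule difference does depend on the reading of the timetable: up to 7 switches against 1 if training runs 16 weeks, or up to 3 against 1 if the 16 sessions are the total. T2 does not bear on three modes versus two, given the stated 2 months per mode.

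A reader might infer that the trial as a whole is compromised. It is not: the comparisons with control, the comparisons among the two-mode arms, the randomisation and the sample size are untouched. What fails is the attribution of a Mixed ABC difference to the third mode.

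**What to change.** In Research objectives and hypothesis, reword the first half of the hypothesis as a comparison of programmes: three modes rotated every 2 weeks in randomised order, against two modes given in sequential 2-month blocks. Add that a difference between Mixed ABC and a two-mode arm will not be attributed to the number of modes alone.

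In the Statistical analysis plan section, state that the three-versus-two contrast rests on T3 and T4, not on T2. T2 can stay in the model for its other purposes.

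The sponsor should also reconcile the 16 sessions at two per week with the 4-month duration, so that the number of blocks in Mixed ABC is clear. Which figure is right is for the sponsor to say.

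The cost is a narrower claim and a few sentences of text. Arms, schedules, sample size and planned models stay as they are.

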### Statistical analysis plan

Data analysis will be performed using the Statistical Package for social sciences (IBM SPSS ver. 27). All data points that were considered outliers, which are out of the interquartile range (IQR) covering the 50% central of samples, will be excluded from analyses. For analyzing program effects, a mixed-effects ANOVA will be used. In this model, there will be a between-subjects factor consisting of five groups (CGs = 0, IGs = 1 to 4) and a within-subject factor consisting of four Trials (Time = 1 to 4). The dependent variables will be the outcome measures of the three cognitive tests and the five physical fitness tests. The independent variables will be time (1 pre-test, 2 post-tests, and 1 follow-up) and intervention (IGs with 4 combinations of training modes & CGs). The participating elderly centre as a cluster will be treated as a random effect. Assumptions (normality, sphericity, etc.) for mixed-effects ANOVA will be tested using an alpha level set as 0.05. The focus of this mixed-effects ANOVA will be mainly on the between-group differences, i.e., the differences among the four IGs. Post-hoc comparisons among IGs will be conducted with Bonferroni correction after finding significant effects. Next, for analyzing specific intervention effects in the 3 treatments crossover design, a similar mixed-effects ANOVA will be used. In this second model, there will be one within-subject factor of four repeated trials (Time = 1 to 4). The dependent variables will be the outcome measures of the three cognitive tests and the four physical fitness tests. The independent variables of time (pre-test, 2 post-tests, and follow-up) and three training modes will be examined by ANOVA with repeated measures. The focus of the second model is to examine the individual effect of the three training modes, so a pre-planned contrast will be conducted to examine their effects. Based on these statistical analyses, results and conclusions will be drawn.

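### At T2 the two-mode arms have had only their first mode, yet T2 counts in the comparison of combinations; that comparison should be tied to T3

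*Protocol article*

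**What the plan says.** **Delivery (Interventions).** Centres in the three two-mode arms "receive an assigned sequential order of two training modes with each mode lasting for 2 months". In Mixed ABC, "participants will receive different training modes every 2 consecutive weeks with randomized order".

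**Visits (Research design).** On the visits during training the article says: "T2 and T3 will be conducted on intervention right after the end of 2-month and 4-month, respectively". The last visit, T4, comes 2 months after training has ended.

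**Hypothesis (Research objectives and hypothesis).** The article expects the following: "participants with the integrated format of three training modes will have higher cognition and fitness scores than the participants with the other combinations". Those other arms each combine two modes.

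**Analysis (Statistical analysis plan).** The first model has five groups and "a within-subject factor consisting of four Trials (Time = 1 to 4"). Its stated emphasis is: "The focus of this mixed-effects ANOVA will be mainly on the between-group differences, i.e., the differences among the four IGs". Follow-up testing is conditional: "Post-hoc comparisons among IGs will be conducted with Bonferroni correction after finding significant effects". A second model addresses the single modes A, B and C. It does not take T2 out of the first model.

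**The concern.** The arms are named for combinations, but at T2 no participant in a two-mode arm has started the second mode. A difference at T2 between, say, the A + B and B + C arms is a difference between whichever modes came first. A difference between Mixed ABC and a two-mode arm sets one mode against half a course of a rotation that may have covered up to three.

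The first model gives T2 the same standing as T3 and T4 and ties no visit to the combination question. A contrast between first modes can therefore contribute to, or trigger, a finding that is then reported as a difference between combinations. Dropping or adjusting for T1 does not remove this, because the problem lies in T2.

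**Working it through.** **1. Exposure at each visit**

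| Visit | Two-mode arms | Mixed ABC |
|---|---|---|
| T1 | none | none |
| T2 (about 8 weeks) | first mode only | 8/2 = 4 two-week blocks; all three modes possible from week 6 |
| T3 | both modes | full course |
| T4 | both modes, 2 months after the end | full course, 2 months after the end |

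Only T3, and T4 as its follow-up, observe the combinations after which the two-mode arms are named.

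**2. The plan's own sample size, to see which test it rests on**

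Inputs from Sample size: f = 0.175, alpha 0.05, power 0.90, rho = 0.5, m = 4 times, k = 5 groups. For the group-by-time interaction, λ = N·m·f²/(1 − rho), with degrees of freedom (k − 1)(m − 1) = 12 and (N − k)(m − 1).

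- The minimum N is 93, or 95 with equal groups. At N = 95, λ = 95 × 4 × 0.030625/0.5 = 23.3 and power is 0.909.
- The design effect is 1 + 14 × 0.1 = 2.4, so 95 × 2.4 = 228, and 228/0.8 = 285.

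All three stated figures reproduce. The 95 is the interaction test; a test of the between-group factor with the same inputs would need 320. The analysis section stresses between-group differences, so both tests are examined below.

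**3. Illustration (assumed values)**

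SD is 1 and rho is 0.5. There are 95/5 = 19 effective participants per arm, so 76 in the four intervention arms. The arms are identical at T1, T3 and T4. At T2 the single-mode effects are A = 0, B = d/2, C = d, and Mixed ABC sits at their mean, d/2.

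*One fixed order per arm (A then B, B then C, C then A).* The T2 means are d/2, 0, d/2 and d. Deviations from their mean are 0, −d/2, 0 and d/2, with sum of squares d²/2.

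- Averaged over four visits, each T2 difference counts as one quarter.
- Group effect: λ = 19 × 4 × (d²/2)/16 ÷ (1 + 3 × 0.5) = 0.95d², on 3 and 72 df.
- Group-by-time: a deviation e at one of four visits leaves an interaction sum of squares of 0.75e², so λ = 19 × 0.75 × (d²/2)/0.5 = 14.25d², on 9 and 216 df.

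*Orders balanced within each two-mode arm.* The T2 means are d/2, d/4, 3d/4 and d/2. The sum of squares falls to d²/8, and the interaction λ to 3.5625d².

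Probability of significance (nominal 0.05):

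| d (SD) | Group-by-time, fixed order | Group effect, fixed order | Group-by-time, balanced |
|---|---|---|---|
| 0.2 | 0.07 | 0.05 | 0.05 |
| 0.3 | 0.09 | 0.06 | 0.06 |
| 0.5 | 0.20 | 0.06 | 0.08 |
| 0.8 | 0.50 | 0.09 | 0.13 |

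These are tests of any difference among the four intervention arms. In this symmetric set-up Mixed ABC equals the average of the two-mode arms at T2, since (0 + d/2 + d)/3 = d/2. The table therefore shows how often a difference among arms is declared. It does not show a bias in favour of Mixed ABC.

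**The case against.** **The interaction test is not wrong in its own terms.** Its null hypothesis is equal profiles over time. If the regimens differ at T2, their profiles do differ, and the visit means would show where. Comparing whole regimens, including a mid-course reading, is a legitimate question. This stands, and it limits the point to what a T2-driven result may be called. It does not remove the point, because the stated hypothesis concerns combinations, and choosing the relevant visit after seeing the profile would be a data-dependent choice.

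**The effect is small at moderate values.** This also stands. At d = 0.3 SD the figures are 0.09 and 0.06 with fixed orders, and 0.06 for the interaction with balanced orders. The 0.50 needs both d = 0.8 SD and fixed orders, and the article does not say whether both orders occur within an arm.

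**A condensed article need not name a primary visit.** True, and the absence alone would be no finding. Here, however, the model, its time levels, its focus and the trigger for post-hoc tests are all stated, and as stated they do not match the hypothesis.

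**T3 is not a clean reading either.** It follows directly on the second mode but comes 2 months after the first. Assume that only C works, by 0.3 SD, and that half is lost in 2 months. A B-then-C arm then shows 0.30 at T3 and a C-then-A arm 0.15, although each had one full course of C. This stands and should be acknowledged in the plan.

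**Stronger readings that the documents do not support.** A reader might infer that T2 always sets three modes against one. The order in Mixed ABC is randomised in a way the article does not describe, so three is possible but not assured. A reader might also picture two arms with the same modes in opposite order that end up alike at T3 but differ on average. No two arms share the same pair of modes, so the trial makes no such comparison.

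**Conclusion.** The point holds in a limited form and should be fixed. The stated schedule and visit times establish that at T2 the two-mode arms have had one mode each, and the stated first model lets that visit count in the comparison of combinations. The separate single-mode model does not correct this.

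The distortion of the time-averaged group effect is modest: d/4, with rejection between 0.05 and 0.09 across the values tried. The group-by-time test is more exposed, at 0.07 to 0.50 with fixed orders and 0.05 to 0.13 with balanced orders. These figures rest on the assumed SD, correlation, effective numbers and pattern of mode effects, and on identical arms at T3 and T4.

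A reader might infer that the main hypothesis could readily be decided by T2 alone, making this a fatal flaw. The figures do not support that: at moderate mode differences the excess over 0.05 is small.

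The stated 16 sessions at 2 per week fill 8 weeks, which does not agree with a 4-month intervention. Those statements must be reconciled, but the exposure at T2 follows from the mode durations and visit times without them.

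**What to change.** In Statistical analysis plan, keep the mixed model, the random centre effect and all four visits, and add the following:

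- The combination hypothesis is tested by contrasts at T3 adjusted for T1, taken from the same model: Mixed ABC against the two-mode arms, and each combination against control.
- T4 is reported as retention of the T3 effect.
- T2 is reported as a mid-course comparison of first modes, and of half a course of Mixed ABC. It is not evidence on combinations.
- T3 comparisons involving two-mode arms can still reflect the order and recency of the modes, and are to be read with that caveat.

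The cost is a change of wording, with no change to visits or data collection. The downside is that the combination contrast no longer pools T2, so it uses fewer observations.
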